Increasing retention in the PMTCT cascade is particularly critical in high-burden, priority countries like Tanzania, where 6.2% of women aged 15-49 are HIV-positive and nearly one quarter of pregnant women living with HIV do not receive ARVs/ART for PMTCT. Notably, in Tanzania, achievements in PMTCT could have important impacts on the national epidemic, as 1 out of every 5 new HIV infections are due to mother-to-child transmission – an estimated 36,225 infections per year. In September 2013, Tanzania began rolling out 'Option B+' to all 6,270 reproductive and child health (RCH) facilities, the PMTCT strategy whereby HIV-infected pregnant women receive ART throughout their lives regardless of clinical stage. By simplifying service delivery, drug regimen, and reducing the number of steps that mothers need to negotiate (such as CD4 testing), Option B+ is expected to improve retention in the PMTCT cascade. However, the postulated benefits of Option B+ are predicated on mothers remaining on lifelong ART, starting at the time of HIV diagnosis. Thus, a critical unresolved issue is whether *asymptomatic* women who learn their HIV status during pregnancy will initiate and adhere to ART under Option B+.

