## 6. 2 Impact and Process Indicators

### Impact Outcomes:

1. Timing of ART initiation: The timing of ART initiation among HIV-infected pregnant women according to gestational age (The number weeks since the first day of the last menstrual period (LMP)). We hypothesize that women in intervention communities will initiate ART earlier than women in comparison communities.
2. Retention in care: Whether an HIV-infected pregnant or postpartum woman on ART is still in care 90 days postpartum (binary 1/0). In Tanzania, postpartum women on ART are typically scheduled for clinical monitoring for their own health at 7, 28, and 42 days (6

week postnatal visit) and then every 30 days thereafter until transfer to the HIV clinic at 18 months. We define retention as a woman who attended her scheduled visit between 60-90 days postpartum.

3. Adherence: We will measure adherence with the medication possession ratio (MPR), the proportion of days when ART was prescribed and an individual is in possession of ART (determined with pharmacy dispensing data). MPR is associated with short-term virologic outcomes. We will determine the proportion of women with MPR  $\geq 95\%$  at 90 days postpartum (binary 1/0).

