## **7. METHODOLOGY**

### *7.1 Definition of Baseline and Endline Cohorts of HIV-Infected Pregnant Women*

We will retrospectively abstract data from routinely collected information in CHW logs and facility registries of patient medical information (see **Figure 1** for an overview of the impact and process outcomes). The research team will collect data from two 6-month cohorts (baseline and endline) of women who are 90 days postpartum to ensure that we can measure retention in care and adherence at 90 days postpartum (**Figure 4**):

- The baseline cohort will include HIV-infected women who were 90 days postpartum between July 1 and December 31, 2014; this corresponds to infants born between April 1 and September 30, 2014. These women are unexposed to the intervention.
- The endline cohort will include HIV-infected women who are 90 days postpartum between May 1 and October 31, 2015, corresponding to infants born between February 1 and July 31, 2015. These women will have been exposed to the intervention during the last 4-9 months of their pregnancy and during their entire 0-90 day postpartum period. This is a reasonable amount of exposure to the intervention given that, on average, women in Tanzania are 5.4 months pregnant at their first ANC visit when they have the initial opportunity to initiate ART.

**FIGURE 4.** Cohorts for Baseline and Endline Data Collection

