All three indicators will be measured primarily from ANC records, though we will also back check these records with CHW logs to ensure accuracy and quality of the data. We will analyze all three measures through difference in difference strategy in order to capture differences in outcome between the control and treatment groups.

**7.5. Evaluation Question #2:** Is the impact of integrating community-based MNCH and PMTCT

*services on retention in care and adherence greater among women who had more contact with CHWs?*

To answer this question, we will monitor the CHW logs to measure (a) the duration of visits with CHWs and (b) the frequency of visits (per week, per month). We will then compare the frequency and duration of visits to each woman's retention in the program, and their level of participation (measured through adherence to ART) to find the correlation between CHW contact and participation.

*7.6. Evaluation Question #3: Is integration of community-based MNCH and PMTCT services acceptable and feasible for CHW, health facility staff, and pregnant and postpartum women, and are there potential spillover benefits on other maternal health outcomes?*

We will conduct a mixed methods process evaluation, including quantitative analysis of process outcomes feedback from stakeholders (two facility personnel, five CHWs, five clients, two Amref staff), and in-depth interviews with women, in order to better understand the effectiveness and feasibility of the intervention. We will focus our efforts on answering the following key questions:

- a. Was the intervention implemented as intended? Was there heterogeneity in implementation? Were standard operating protocols followed consistently and correctly?
- b. Were there community- or facility-level factors that influenced the success of the intervention? Was the intervention impeded by the time availability of CHW or facility staff?
- c. Did the intervention motivate pregnant and postpartum women? How? What aspects were motivating and why? Did the intervention inadvertently increase stigma?
- d. What were successful or challenging aspects of the intervention throughout the causal chain (**Figure 1**)? What could be improved?

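### Outcome 1 (gestational age at ART start) uses an endline cohort built for 90-day outcomes, so some ART starts before launch are scored as endline values and modestly dilute the timing effect

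*Protocol*

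**What the plan says.** Protocol section 7.1 defines two cohorts by the date on which women are 90 days postpartum. The reason given is "to ensure that we can measure retention in care and adherence at 90 days postpartum"; the timing of ART is not mentioned. For the later cohort: "The endline cohort will include HIV-infected women who are 90 days postpartum between May 1 and October 31, 2015". The matching birth window is 1 February to 31 July 2015. On exposure it says "These women will have been exposed to the intervention during the last 4-9 months of their pregnancy" and adds the whole period from birth to day 90. It calls this exposure reasonable because "on average, women in Tanzania are 5.4 months pregnant at their first ANC visit when they have the initial opportunity to initiate ART".

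Section 6.2 makes the first impact outcome "The timing of ART initiation among HIV-infected pregnant women according to gestational age", and section 6.3 lists ART initiation among the primary outcomes. Section 7.4 applies one analysis to timing, retention and adherence: "We will analyze all three measures through difference in difference strategy". Nothing in sections 6.2, 7.1, 7.3 or 7.4 requires an endline ART start to fall after launch, or the woman to be off ART at launch. The readable text gives no calendar launch date; Figure 4 is not shown and may contain it.

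**The concern.** Retention and adherence are observed after birth, so selecting women by their day-90 date suits them: every endline woman has her whole postpartum period after launch. Gestational age at ART start is fixed months earlier. By the protocol's own figures, the first women in the endline window were about five months pregnant at launch, and the average first chance to start ART comes at 5.4 months. Women in that part of the window who booked somewhat earlier than average could already have been on treatment.

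Such starts occur in both arms and carry no information about the intervention. They pull the endline difference between arms, and so the difference-in-differences estimate, toward zero. They are also the earliest starts among the women concerned, on an outcome whose hypothesis is earlier initiation.

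**Working it through.** **Launch implied by section 7.1.** Endline births run from 1 February to 31 July 2015.
- From the 4-month end: 1 February 2015 minus 4 months is 1 October 2014.
- From the 9-month end: 31 July 2015 minus 9 months is about 1 November 2014.

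The 1 October date fits the range better. A 1 November launch leaves the earliest births only about 3 months of exposure, so it is the late limit.

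**Inputs from the protocol.** The birth window above, and a mean of 5.4 months at first ANC: 5.4 × 30.44 / 7 = 23.5 weeks.

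**Assumed, because the protocol does not give them.** Births uniform over the window, gestation of 40 weeks, ART start at the first ANC visit, a normal distribution of that visit with SD 4, 6 or 8 weeks, and a true advance of 4 weeks.

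**Gestation at launch** = 40 − (birth date − launch date in days) / 7.
- Launch 1 October 2014: 40 − 123/7 = 22.4 weeks for a 1 February birth; 40 − 303/7 = −3.3 weeks for a 31 July birth (not yet pregnant).
- Launch 1 November 2014: 40 − 92/7 = 26.9 weeks; 40 − 272/7 = 1.1 weeks.

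**Share of starts before launch** = average over birth dates of Φ((gestation at launch − 23.5) / SD).

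**Dilution** was simulated. Starts before launch stay where they are. Later starts move 4 weeks earlier, but not to before launch. Dilution = 1 − mean realised advance / 4.

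| Launch | SD (weeks) | Starts before launch | Dilution, all women | Dilution, women not on ART at launch |
|---|---|---|---|---|
| 1 Oct 2014 | 4 | 4.5% | 9% | 4% |
| 1 Oct 2014 | 6 | 7.5% | 12% | 4% |
| 1 Oct 2014 | 8 | 10.5% | 14% | 4-5% |
| 1 Nov 2014 | 4 | 15% | 22% | 8% |
| 1 Nov 2014 | 6 | 17% | 23-24% | 7% |
| 1 Nov 2014 | 8 | 20% | 26% | 7% |

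With a 1 October launch, the share before launch among February births alone is 24-36%, so the problem sits at the start of the window.

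In weeks, an intended 4-week advance appears as about 3.4 to 3.7 weeks for a 1 October launch and about 3.0 to 3.1 weeks for 1 November.

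The last column shows what the proposed restriction achieves. Some dilution remains because a woman due to start within 4 weeks after launch can advance only as far as launch.

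**Illustration.** A woman delivering on 10 February 2015 has an LMP of 6 May 2014 at 40 weeks. If she starts ART at 20 weeks, the date is 23 September 2014, before a 1 October launch, yet the plan records 20 weeks as an endline value. The example lies close to the inferred date; the table, not the example, carries the argument.

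**The case against.** The strongest reply is that section 7.1 has already considered initiation. It cites the 5.4-month figure, and with a 1 October launch even the earliest births were at about 5.0 months, so the average woman's first opportunity follows launch. That is correct for the average woman. It does not cover early bookers in the first part of the window, and with a 1 November launch the earliest births are already past 5.4 months.

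The shares also rest on assumptions. Section 6.1 includes postpartum women in the timing question, and starts later than first ANC would lower the shares. Working the other way, under Option B+ "HIV-infected pregnant women receive ART throughout their lives regardless of clinical stage", so some women may have been on ART before conception, which would raise them. The protocol gives a figure for neither.

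One may say that dilution is conservative and that risk sets belong in the SAP. Dilution does not produce false positives, but it does bias a primary outcome, and it is the protocol itself that fixes the cohort and defends its exposure.

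Excluding women by ART start date might look like selecting on the outcome. ART status on a single calendar date at launch precedes the intervention in both arms, so the comparison between arms remains valid. Restricting by gestation at launch is also valid but costs more: keeping only births from 1 May 2015 would lose roughly half of the endline timing sample.

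A reader might infer something stronger: that launch was in December 2014 or January 2015, since section 7.1 calls baseline women unexposed while their day-90 dates run to 31 December 2014, and hence that a real effect could vanish. The documents do not support this. Those dates would leave February births about 2 months or 1 month of exposure in pregnancy, against a stated minimum of 4. The conflict over the baseline cohort's exposure is a separate matter to reconcile; it mainly concerns retention and adherence and should not be used to enlarge this point.

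**Conclusion.** The point holds as a modest bias toward zero in outcome 1 only. As written, the plan counts ART starts that the intervention could not have influenced. Across the launch dates that section 7.1 implies, and under the distributional assumptions listed above, this is about 5-20% of endline starts, with about 9-26% dilution of a 4-week advance. At the better-fitting 1 October date the figures are about 5-11% and 9-14%. Women on ART before conception would add an unknown amount. The figures do not support saying that a real shift would be reported as null. Retention, on which the study is powered, and adherence are not affected. The correction is worth making because it is cheap and outcome 1 is primary.

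**What to change.** In sections 6.2 and 7.1, state the calendar launch date and restrict the outcome 1 analysis to women not yet on ART on that date, using the same date in both arms. Apply the mirrored date 10 months earlier to the baseline cohort, since the birth windows open on 1 April 2014 and 1 February 2015. For a 1 October 2014 launch that is 1 December 2013. Both cohorts are then truncated alike and the difference-in-differences compares like with like.

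Report the full postpartum-anchored cohort as a sensitivity analysis and, optionally, a restriction by gestation at launch. Keep the existing cohorts for retention and adherence, and limit the statement that exposure is reasonable to those two outcomes.

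The cost is protocol wording and a date comparison using ART start dates that outcome 1 already requires. About 5-20% of endline timing observations are lost under the assumptions above, so the interval for outcome 1 widens somewhat, and its result then applies to women not yet on ART at launch. In return, dilution falls to about 4-8%.

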**2014**

[figure not shown]

**2015**

[figure not shown]

## 7.2. Data Sources

Data will be abstracted from the following sources, using the woman's clinic identification number (clinic ID) as the unique code to link across data sources:

- **CHW logs:** CHWs maintain standardized logs of pregnant and postpartum women in their catchment area. At the start of the study, we will modify the log form to include women's clinic ID. We will retrospectively abstract the clinic ID along with demographic data about both HIV-infected and uninfected women in the baseline or endline cohorts, as CHW in comparison villages may not know women's HIV serostatus. Note that this is a significant strength of our study, as we will have a community-based measure of pregnant women, including women who do not utilize RCH services.
- **ANC register:** Contains information about all women who booked for ANC, including number of visits, HIV testing results, health facility delivery, and attendance at the postnatal visit. We will abstract these data for each woman in the baseline or endline cohort and match their health information with CHW log information.
- **ART register:** Contains information about HIV-infected pregnant or postpartum women who are initiated on ART at RCH clinics. For all HIV-infected women in the baseline or endline cohorts, we will match them to the ART register to determine whether they initiated ART and attended visits.
- **CTC2 Cards:** Contains individual medical record data for HIV-infected women. We will abstract data from these cards as needed, to supplement data in the ART register.
- **Pharmacy logbook:** Contains ART pick-up dates and quantity for HIV-infected women.

**Table 1.**

| Evaluation Question                     | Data Sources               | Outcome / Indicator(s)   |
|-----------------------------------------|----------------------------|--------------------------|
| 1. Impact of the intervention on:       |                            |                          |
| a. timing of ART initiation             | ART register
CTC2 cards | Timing of ART initiation |
| b. retention in care 90 days postpartum | ART register               | Numerator:HIV-Infected   |

|                                                          |                            |                                                                                                                               |
|----------------------------------------------------------|----------------------------|-------------------------------------------------------------------------------------------------------------------------------|
|                                                          | CTC2 cards
CHW register | women retained in care at 90 days postpartum
Denominator: HIV-infected pregnant women                                      |
| c. adherence to ART 90 days postpartum                   | Pharmacy logbook           | ART adherence (MPR)                                                                                                           |
| 2. Impact heterogeneity by intensity of exposure to CHWs | CHW logs                   | Number of CHW visits to individual women                                                                                      |
| 3. Acceptability and feasibility                         | ANC register               | ≥4 ANC visits
facility delivery
postnatal visit attendance
EID testing
Denominator: HIV-infected postpartum women |

### 7.3 Sampling and Data Collection

For many of the impact and process outcomes, we will use ANC logs to abstract data from the women who will comprise the denominator (e.g., proportion of women retained in care 90 days postpartum). Once we identify these women through the health records, we can use their medical ID to find CHW logs. The logs will provide us with further details of the services provided to each woman.

In some health facilities, electronic medical records will be available and we will not have to sample a subset of women. However, in others the records will be fully paper based and we will have to sample women for data abstraction. In health facilities where there are <50 HIV-infected pregnant or postpartum women in the baseline or endline cohorts (determined with the CHW log and ANC register), we will abstract data from the ART register on all women. At health facilities where there are ≥50 HIV-infected pregnant or postpartum women in the cohorts, we will abstract a predetermined sampling fraction such that 75% of women are sampled from cohorts with 50-100 women, 50% of women are sampled from cohorts with 100-200 women, etc. This approach will ensure that the sample size is adequate to detect a minimum increase in retention in care at 90 days postpartum. In facilities where data are manually abstracted from paper records, we will use Qualtrics Offline Surveys on Android tablets.

In facilities with 50 or more HIV-infected pregnant women in the baseline or endline cohorts, we will use a systematic random sampling procedure with a random start. Research assistants will select a number from a random number table and then select the woman in this position for the study. The research assistant will then sample every  $k$  eligible woman thereafter, where  $k$  is the sampling fraction, described above.

**7.4. Evaluation Question #1:** What is the impact of integrating community-based MNCH and PMTCT services using CHWs in Shinyanga, Tanzania on:

- a. The timing of ART initiation among HIV-infected pregnant and postpartum women;
- b. Retention of HIV-infected women in care 90 days postpartum; and
- c. Adherence to ART at 90 days postpartum.

All three indicators will be measured primarily from ANC records, though we will also back check these records with CHW logs to ensure accuracy and quality of the data. We will analyze all three measures through difference in difference strategy in order to capture differences in outcome between the control and treatment groups.

**7.5. Evaluation Question #2:** Is the impact of integrating community-based MNCH and PMTCT

*services on retention in care and adherence greater among women who had more contact with CHWs?*

To answer this question, we will monitor the CHW logs to measure (a) the duration of visits with CHWs and (b) the frequency of visits (per week, per month). We will then compare the frequency and duration of visits to each woman's retention in the program, and their level of participation (measured through adherence to ART) to find the correlation between CHW contact and participation.

*7.6. Evaluation Question #3: Is integration of community-based MNCH and PMTCT services acceptable and feasible for CHW, health facility staff, and pregnant and postpartum women, and are there potential spillover benefits on other maternal health outcomes?*

We will conduct a mixed methods process evaluation, including quantitative analysis of process outcomes feedback from stakeholders (two facility personnel, five CHWs, five clients, two Amref staff), and in-depth interviews with women, in order to better understand the effectiveness and feasibility of the intervention. We will focus our efforts on answering the following key questions:

- a. Was the intervention implemented as intended? Was there heterogeneity in implementation? Were standard operating protocols followed consistently and correctly?
- b. Were there community- or facility-level factors that influenced the success of the intervention? Was the intervention impeded by the time availability of CHW or facility staff?
- c. Did the intervention motivate pregnant and postpartum women? How? What aspects were motivating and why? Did the intervention inadvertently increase stigma?
- d. What were successful or challenging aspects of the intervention throughout the causal chain (**Figure 1**)? What could be improved?

The interview and focus guides will be developed to align with constructs from the theory of change to understand how the intervention works or does not work. For example, we will ask women about their perceptions of the process outcomes (ANC, facility delivery, postpartum visit attendance) before and after their pregnancy and how the Action Birth Card did or did not influence their behavior to engage/not engage in these services. Furthermore, among HIV infected women, we will probe about the process of initiating ART, coming to terms with lifelong treatment, PMTCT, and how they think about remaining on ART after delivery. We will then apply the lens of the intervention to understand whether the ABC or CHW interaction altered their expectations, preferences, or behaviors. Together, these data will help to triangulate our results from the quantitative analysis.

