3. Tracing of treatment defaulters: At their monthly meetings with RCH staff, CHWs will review the ART register to identify women who missed scheduled appointments and those who are lost to follow-up according to the local definition: non-attendance at three successive scheduled appointments with two unsuccessful follow-up attempts. CHWs will attempt to contact these women via mobile phone or home visit and re-engage them in care. CHWs will provide updates to the clinic about their progress and will coordinate tracing activities with those of the clinic (if any).
4. Adherence counseling for HIV-infected women on ART: CHWs will use the existing adherence counseling manual used by community-based home based care volunteers for people living with HIV, with additional messaging customized for asymptomatic women (as many recently diagnosed pregnant women will be asymptomatic). Adherence counseling will be conducted during the monthly CHW home visits.

The intervention’s theory of change is shown below in **Figure 1**, including the process and impact indicators that will be measured as part of the impact evaluation. Currently, CHWs in Shinyanga Region (and elsewhere in Tanzania) refer pregnant women to ANC in addition to other health promotion activities. Once registered for ANC, pregnant women may or may not complete the services in the PMTCT cascade, including starting and adhering to ART (if HIV-infected), and they may disengage and re-engage in care. In the current study, we will implement an intervention to integrate community-based MNCH services and PMTCT using CHWs. We hypothesize that this approach will result in HIV-infected pregnant and postpartum women initiating ART earlier as well as better retention in care and improved adherence.

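### Section 7.4 takes all three impact outcomes from ANC records that, as described, cannot supply them, and leaves open whether CHW logs, probably better informed in the intervention arm, may change an outcome

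*Protocol*

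**What the plan says.** Section 7.4 of the Protocol gives one measurement rule for the three impact outcomes: "All three indicators will be measured primarily from ANC records, though we will also back check these records with CHW logs to ensure accuracy".

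Other sections say something different:

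- Section 6.2 defines retention as attending the scheduled visit between 60 and 90 days postpartum. It defines adherence as a medication possession ratio (MPR) of at least 95%, "determined with pharmacy dispensing data".
- Section 7.2 describes the ANC register as covering women who booked, "including number of visits, HIV testing results, health facility delivery, and attendance at the postnatal visit". For HIV-infected women it says "we will match them to the ART register to determine whether they initiated ART and attended visits". Drug pick-up dates and quantities are in the pharmacy logbook.
- Table 1 gives the ART register and CTC2 cards for timing. For retention it gives the ART register followed by "CTC2 cards CHW register", and for adherence the pharmacy logbook. The ANC register appears only under Question 3.

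On what CHWs know, section 4 says that CHWs in Shinyanga currently take no part in HIV care for pregnant women, PMTCT or Option B+. Section 5 has intervention CHWs review the ART register monthly, trace women who missed appointments and give adherence counselling; "CHWs will provide updates to the clinic about their progress". Section 7.2 explains why logs are abstracted for infected and uninfected women alike: "as CHW in comparison villages may not know" a woman's serostatus.

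**The concern.** There are two problems. One is certain and one is conditional.

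The certain one is that an abstractor cannot follow both 7.4 and Table 1. Retention is the outcome on which the study is powered, and its source is stated in two incompatible ways.

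The conditional one is that the CHW log is not a neutral check. The people who deliver the intervention keep it, and their contact with HIV care differs by arm because of the intervention. The protocol does not say what happens when a log and a clinic record disagree. If a log entry could turn a non-attender into a retained woman, or the reverse, the measuring instrument would differ between arms at endline. Difference-in-difference removes arm differences that are stable over time. It does not remove one that appears in a single arm in the second period.

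**Working it through.** **Step 1: sources side by side.**

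| Outcome | Needs (6.2) | Source in 7.2 and Table 1 | Source in 7.4 |
|---|---|---|---|
| Timing of ART start | Gestational age when ART started | ART register, CTC2 cards | ANC records, CHW back-check |
| Retention | Scheduled visit attended at 60-90 days | ART register, CTC2 cards; Table 1 adds CHW register | ANC records, CHW back-check |
| Adherence | Dispensing data for MPR | Pharmacy logbook | ANC records, CHW back-check |

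The only postpartum item in the ANC register as described is the postnatal visit. Section 6.2 places the 6-week postnatal visit at day 42, before the window opens at day 60. With 30-day spacing the next visit falls at day 42 + 30 = 72, and the ANC register is not said to record it. On its stated content, the ANC register supplies none of the three outcomes.

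**Step 2: what the logs are said to contain.** Clinic ID and demographic data (7.2), services provided to each woman (7.3), and duration and frequency of CHW visits (7.5). No section says that they record ART clinic attendance. That intervention logs will hold more about HIV care is an inference from sections 4, 5 and 7.2, though a reasonable one.

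**Step 3: the plan's own figure.** Section 6.4 uses 67% against 80%, ICC 0.05, 15 communities per arm, 36 women each and 80% power. Alpha is not stated; I assume two-sided 0.05. The continuity-corrected two-proportion formula gives 195 per arm. The design effect is 1 + (36 - 1) x 0.05 = 2.75, and 195 x 2.75 = 536.25, which rounds up to the stated 537 per arm. These inputs can therefore be used below.

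**Step 4: illustration with no true effect.** Set true retention at 67% in both arms and both cohorts. In the intervention arm at endline only, let the log move a share *a* of apparent non-attenders to retained and a share *b* of apparent attenders to not retained. Then

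false difference-in-difference = 0.33*a* - 0.67*b*.

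Both shares are assumptions; the protocol gives neither.

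| *a* (with *b* = 0) | False difference | Share of 13 points | Chance of p < 0.05, endline comparison | Chance of p < 0.05, difference-in-difference |
|---|---|---|---|---|
| 0% | 0 | 0% | 5% | 5% |
| 5% | 1.65 points | 13% | 6% | 6-7% |
| 10% | 3.3 points | 25% | 11% | 8-13% |
| 20% | 6.6 points | 51% | 30% | 17-40% |

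The chances use a normal approximation with 36 x 15 = 540 women per arm and cohort. For the endline comparison the effective size is 540 / 2.75 = 196.4 per arm. For difference-in-difference, the variance of an arm's mean change is the sum over the two periods of p(1 - p) x 2.75 / 36, less 2 x CAC x 0.05 x the geometric mean of the two p(1 - p), all divided by 15. CAC is the cluster autocorrelation, run from 0 to 1. For *a* = 10% the standard error is 0.0666 at CAC 0 (0.033 / 0.0666 = 0.50, giving 8%) and 0.0392 at CAC 1 (0.033 / 0.0392 = 0.84, giving 13%).

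The direction is not fixed. With *a* = 10% and *b* = 5%, the result is 3.3 - 3.35 = -0.05 points, practically nil. With *a* = 0 and *b* = 5%, it is -3.35 points.

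**The case against.** The strongest reply has four parts.

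- **ANC records may be shorthand** for everything held at the RCH clinic, including the ART register. That would soften the contradiction, but section 7.2 lists the ANC register, ART register, CTC2 cards and pharmacy logbook as separate sources, and Table 1 keeps them separate. The wording still needs correcting.
- **Back-checking is described as a quality measure, not an override.** A reader might infer that the plan will create a retention difference. The protocol does not support that: it nowhere says that a log entry replaces a clinic record, or that logs hold ART attendance, and the tracing updates go to the clinic. A home visit would not itself meet the retention definition. This stands, and it limits the point to a risk that the protocol leaves open.
- **The CHW register in row 1b may serve the denominator**, since section 7.2 values the logs as a community-based count that includes women who do not use RCH services. This is possible, but section 7.3 draws denominators from ANC logs, and the 7.4 back-check covers the indicators themselves.
- **Baseline linkage.** Section 7.2 says "At the start of the study, we will modify the log form to include" the clinic ID, from which a reader might infer that baseline logs cannot be linked. The next sentence plans to abstract the clinic ID retrospectively for both cohorts. Feasibility is a fair question; impossibility is not established.

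**Conclusion.** The source rule in 7.4 is wrong as written. It conflicts with 6.2, 7.2 and Table 1, and the ANC register as described cannot supply ART start, the 60-90 day visit or MPR. That conclusion needs no assumption.

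The ascertainment risk is real but conditional. It requires that log entries be allowed to change outcomes and that logs say more about HIV care in the intervention arm at endline. The second is likely; the first is not stated. A reader might conclude that logs are informative in the intervention arm only. The text supports less: comparison CHWs may not know serostatus, which is not the same as never knowing it. Nor are 3.3 or 6.6 points estimates of bias. They follow from assumed, one-way reclassification of 10% or 20%, and the true size and sign are unknown. What can be said is that, if such a bias arose, difference-in-difference would carry it through in full. The sample size is not affected.

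**What to change.** - Correct 7.4 to agree with 7.2 and Table 1: classify ART start and retention from the ART register and CTC2 cards, and MPR from the pharmacy logbook, by the same rule in both arms and both cohorts.
- State that CHW logs change no outcome classification. Use them for Question 2 exposure and to describe the community. Report any disagreement between log and clinic record by arm, without altering outcomes.
- In Table 1 row 1b, remove the CHW register as a numerator source, and reconcile the denominator source with 7.3, which uses ANC logs.

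The cost is protocol wording; no new data are collected and the stated sample size stays. There are three downsides to acknowledge. Visits known only to CHWs go uncounted. Women who never book ANC stay outside the denominator, as 7.3 already implies. And facility recording may still differ in quality between arms, because intervention CHWs work with clinic staff on the ART register; a common rule does not guarantee equal ascertainment.
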